#### Analysis of baseline data

Descriptive statistics will be used to summarize participants’ demographic characteristics. Continuous variables will be expressed as mean ± SD, whereas categorical variables will be reported as frequency and percentages. To compare baseline characteristics between participants who withdraw and those who complete the study, we will use *t* test for continuous variables and χ^2^ test for categorical variables.

#### Statistical hypotheses

At the individual level, the null hypothesis is that there is no difference in PBGP responses between any 2 staple foods for each participant, and the alternative hypothesis is that such differences exist. At the population level, the null hypothesis is that there is no difference in the average effect of PBGP induced by any 2 staple foods, and the alternative hypothesis is that such differences exist.

#### Individual-level N-of-1 trial analysis

To assess the PPGR to various staple foods at an individual level, Bayesian model will be performed. It is presupposed that individual observations of PBGP and iAUC_3h_ adhere to a normal distribution centered on each participant’s true average effect. The MCMC method will be used to estimate the posterior distribution of the parameters of interest. We will initiate 4 chains, with each executing 4000 iterations, culminating in a total of 16,000 sampling iterations. The Bayesian inference will be executed using the following equation for PBGP:(1)$${\text{PBGP}}_{i}=\beta_{0}+\sum_{j}\beta_{j}\cdot {\text{staple}\;\text{food}}_{j}+\epsilon_{i}$$in which the PBGP for participant *i* is modeled as the intercept, with the effect of each staple food *j* denoted as the intervention effect, and the random error for individual *i* modeled as a normal distribution with a mean of 0 and a large SD. Noninformative prior distributions will be incorporated into the model due to uncertainty regarding prior knowledge. Following the estimation of the posterior distribution of the effect of each staple food within the Bayesian model, the average value of the posterior distribution for differences between foods will be calculated, alongside the SE and 95% credible intervals. Standard procedures for warm-up periods, diagnostics for model convergence and stability, and residual checks will be applied. During the warm-up period, initial samples will be discarded to allow the chain to converge to a stationary distribution. The Gelman-Rubin test will be used to assess the convergence of the MCMC chains, with an *R*-hat value of <1.05, indicating that the chain has converged. The threshold for posterior probabilities will be set at 80% [28].

For a comprehensive evaluation of the PPGR of various staple foods among patients with diabetes, a weighted average response probability will be generated for each staple food. Using Bayesian models and sequentially using each staple food as a reference, we will estimate the posterior probability that the average difference between the reference food and the other 4 staple foods exceeds the MCID. As mentioned earlier, in this study, we define the MCID for PBGP as 0.78 mmol/L, and the MCID of iAUC_3h_ is 106.78 mmol/L·min, representing 10% of the difference between patients with T2DM and those with impaired fasting glucose, a difference that amounts to 1067.85 mmol/L·min [29].

For PBGP, the weighted glycemic response score (WGRS) for each staple food is calculated using the following equation:(2)$${\text{WGRS}}_{i,j}=\frac{\sum_{k\neq j}{P\left({\Delta \text{PBGP}}_{i,j}>0.78\right)}_{k}\cdot \frac{1}{{\text{CV}}_{k}}}{\sum_{k\neq j}\frac{1}{{\text{CV}}_{k}}}$$

Equation 2 computes the sum of the posterior probability that, for participant *i*, the average difference between staple food j and other staple foods *k* exceeds the MCID of 0.78 mmol/L across multiple comparisons, divided by the coefficient of variation (CV) of each staple food *k*, which serves as a weight adjustment [30]. The result is then normalized by the sum of the reciprocals of the CVs. The WGRS of each staple food quantifies the probability of a clinically significant higher PBGP for that food across multiple comparisons. In the context of achieving a more stable glucose response, particularly in patients with diabetes, a staple food with a higher WGRS is less desirable.

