### Sample size estimation

In this study, the primary outcome, PBGP, was reported at the population level using a Bayesian hierarchical model. Given the absence of formulas for sample size calculation in this type of population design, the sample size calculation in this study referred to the simulation method based on the Bayesian hierarchical model conducted by Stunnenberg et al. [23]. Additionally, the statistical power under different sample sizes was evaluated via the Markov Chain Monte Carlo (MCMC) method. The minimum clinically important difference (MCID) is an indicator used to assess the clinical significance of changes in medical outcomes [24]. It represents the smallest change in clinical outcomes that is considered meaningful by patients, clinicians, or researchers. Referring to the study by Tian et al. [25], the MCID of PBGP in this study was defined as 0.78 mmol/L, which was determined based on a 20% difference in PBGP between patients with T2DM and those with impaired fasting glucose, i.e., 3.89 mmol/L [26]. According to previous studies, the difference in PBGP between patients with diabetes consuming white rice and pasta was 2.4 mmol/L, with a between-individual SD of 2.5 mmol/L and a within-individual SD of 1.2 mmol/L [21]. At the individual level, it was assumed that the true intervention effect of each participant followed a normal distribution; at the observation level, the within-individual variation was set to be the same. Observational data for each subject were randomly generated through simulation involving 3 intervention cycles and 5 staple foods, and a Bayesian hierarchical model was constructed based on these data.

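### Equation 1 gives the residual error a large SD, which conflicts with the protocol's own within-person SD of 1.2 mmol/L and reads like a coefficient prior attached to the wrong term

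*Protocol article*

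**What the plan says.** The section on the individual-level N-of-1 analysis gives Equation 1: PBGP for participant i equals an intercept plus a sum of staple-food effects plus an error carrying only the index i. The error is "modeled as a normal distribution with a mean of 0 and a large SD". No value for that SD follows.

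The next sentence deals with priors as a separate matter: "Noninformative prior distributions will be incorporated into the model due to uncertainty regarding prior knowledge". It does not list the parameters concerned. Earlier in the section, the observations are said to "adhere to a normal distribution centered on each participant’s true average effect". The section also promises that "diagnostics for model convergence and stability, and residual checks will be applied".

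Two figures in this section determine how an individual result is read: "The threshold for posterior probabilities will be set at 80" percent, and "we define the MCID for PBGP as 0.78 mmol/L".

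The sample size section supplies the planning values. For the effect, it states that "the difference in PBGP between patients with diabetes consuming white rice and pasta was 2.4 mmol/L". The variability assumed in that same section is given in these words: "with a between-individual SD of 2.5 mmol/L and a within-individual SD of 1.2 mmol/L". Its simulation uses 3 cycles of 5 foods per participant.

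**The concern.** In a model fitted to one participant, the residual is the variation between repeated meals of the same food in that person. The sample size section describes the same quantity as 1.2 mmol/L, which is not large beside a planning difference of 2.4 mmol/L. The two sections therefore do not agree. Nothing in the individual-level section says that the residual SD is estimated from the data. Variance priors are mentioned only for the population-level model.

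The notation does not settle the matter. With i defined as the participant and no index for meal or period, Equation 1 shows one outcome and one error per person. The repeats that would identify the residual SD do not appear in it.

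The residual SD governs every individual output: the credible intervals, the probability that a difference exceeds the MCID, and whether 80% is reached. The weighted glycemic response score (Equation 2) is an average of those probabilities. That score is then the dependent variable in the microbiota analysis and, according to the Discussion, the basis of each patient's dietary recommendation. An SD that is too large pulls all these probabilities toward 50%.

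**Working it through.** **The plan's own figure.** The protocol states no figure for Equation 1. The nearest is the population-level result at n = 14: power 86.0% and type I error 2.0%. A flat-prior approximation, taking 2.5 as the between-person SD of the food difference, gives SE = √((2.5² + 2 × 1.2²/3)/14) = 0.718. Success then requires an estimate above 0.78 + 0.8416 × 0.718 = 1.38, which gives power 92.2% and type I error 2.7%. Of the other ways tried of entering the SDs, none matched both published figures. This mismatch is not evidence on the present point, because it concerns a different model whose priors and number of simulation runs are not given.

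**Inputs for one participant**
- Observed difference d = 2.4 mmol/L, the planning difference for white rice and pasta (sample size section).
- MCID 0.78 mmol/L and threshold 80% (individual-level section).
- 3 meals per food and 5 foods, so 15 observations and 15 − 5 = 10 residual degrees of freedom.
- Residual SD: 1.2 mmol/L (sample size section). All other values of s below are assumptions.

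**If the SD is held at a value s** (flat coefficient priors):
- Posterior SD of a food difference = s × √(2/3)
- P(difference > 0.78) = Φ((2.4 − 0.78)/(s√(2/3)))
- Observed difference needed for 80% = 0.78 + 0.8416 × s√(2/3)
- 95% half-width = 1.96 × s√(2/3)

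| s (mmol/L) | Posterior SD | P at d = 2.4 | Difference needed for 80% | 95% half-width |
|---|---|---|---|---|
| 1.2 | 0.98 | 0.951 | 1.60 | 1.92 |
| 2.36 | 1.93 | 0.80 | 2.40 | 3.78 |
| 5 (assumed) | 4.08 | 0.654 | 4.22 | 8.0 |
| 10 (assumed) | 8.16 | 0.579 | 7.65 | 16.0 |
| 30 (assumed) | 24.49 | 0.526 | 21.4 | 48.0 |
| 100 (assumed) | 81.65 | 0.508 | 69.5 | 160 |

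The break-even SD at d = 2.4 is 1.62/(0.8416 × √(2/3)) = 2.36.

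**If the SD is estimated**, with prior 1/σ and sample value 1.2, the posterior of a difference is t with 10 df and scale 1.2 × √(2/3) = 0.98. Then P at d = 2.4 is 0.935. The difference needed for 80% is 0.78 + 0.879 × 0.98 = 1.64, and the half-width is 2.228 × 0.98 = 2.18. This row, not the fixed-1.2 row, is the proper comparator for a corrected plan.

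**Share of participants reaching 80% for this pair.** Observed differences are taken as normal with mean 2.4 and SD √(2.5² + 2 × 1.2²/3) = 2.685. About 61% reach the threshold when σ is estimated, about 25% at a fixed SD of 5, 2.5% at 10 (a 30% chance of at least 1 of 14), and essentially none at 30 or more.

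**The case against.** The strongest reply is that this is a misplaced phrase and not a decision about the model. The text never says that the SD is held constant, and it gives no number, which a fixed SD would need. Noninformative priors follow in the next sentence, and MCMC is used for the parameters of interest. A normal with mean 0 and a large SD is how one usually describes a vague coefficient prior. This stands, and it is the likelier explanation.

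A reader might infer that the protocol fixes the residual SD and that no participant could then reach 80%. The documents do not support this. Nothing states that the SD is fixed, and the claim needs an assumed SD of about 30 or more; at 5, about a quarter of participants would still reach the threshold.

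A reader might also infer from the missing index that the repeated meals are left out of the analysis. That goes too far. The study procedures set 3 periods of 5 test days, the sample size simulation uses them, and the individual-level section speaks of individual observations. The index is missing from the notation, but the repeats are plainly meant as data.

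The population-level model is described separately, includes within-person variation and has noninformative variance priors. The planned residual checks might also expose a residual SD far out of line with the data. Both limit the reach of the problem. Neither corrects the sentence beside Equation 1, which is a positive statement of the model and not a detail left to another document.

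**Conclusion.** The description of the error in Equation 1 is wrong or, at best, ambiguous. It conflicts with the within-individual SD of 1.2 mmol/L, and no individual-level text says that the residual SD is estimated. It should be corrected before analysis, because the individual analysis cannot be reproduced as described.

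The size is conditional. Taken literally, any fixed SD above about 2.36 mmol/L leaves the protocol's own planning difference short of 80%, and the probability falls to 0.65 or 0.58 at SDs of 5 or 10, against about 0.94 with an estimated SD of 1.2. These results rest on flat coefficient priors, 3 meals per food and a common residual SD across foods. The shares of participants also rest on reading 2.5 as the between-person SD of the difference. If the phrase is only a slip and the code estimates σ, the numerical results are unaffected and the defect is confined to the published model statement.

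**What to change.** Write Equation 1 for participant i and test meal t:

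PBGP_it = β_0i + Σ_j β_ij × food_jt + e_it, with e_it ~ N(0, σ²) and the sum over the foods other than the reference.

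Add that σ is estimated from that participant's 15 meals, and name its prior. The protocol's noninformative choice is acceptable: the 1/σ prior used above gives usable results on 10 df, and a prior scaled to 1.2 mmol/L would be a preference and not a requirement. Assign the normal with mean 0 and large SD to the coefficients only, and give its value. Confirm that the analysis code agrees with the corrected text.

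The cost is one rewritten equation and a sentence or two, with no change to visits, meals, sample size or data collection.

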**Discussion:**

By using the *N*-of-1 trial methodology, this study is anticipated to reveal substantial interindividual variations in PPGR and to identify staple foods that are most effective in stabilizing blood glucose concentrations for individual patients, providing insights into personalized nutritional management for T2DM.

This trial was registered at Chinese Clinical Trial Register as ChiCTR2400090138 (24 September, 2024).

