### Study procedures

The study scheme is outlined in Figure 1. The study consists of 3 periods, each of which comprised 5 test days. On each test day, a different test diet will be consumed for breakfast. Within each period, the 5 test diets will be administered in a randomized sequence. By referring to the washout period duration (48 h) in previous studies by Zavitsanou et al. [21] and considering that key indicators such as postprandial blood glucose-related parameters can return to baseline concentrations within 2–3 d (thus effectively eliminating the residual effects of the dietary used in the previous test), a 3-d washout period was set between each test in this study. During the washout period, subjects were instructed to maintain their regular dietary habits [21,22]. To ensure consistency across test diets and to minimize the impact of prior dietary intake, participants will be advised to restrict their consumption of high-protein, high-fat, and high-fiber foods on the day preceding the test day. Additionally, they will be provided with a balanced dinner on the evening before the test day and will be required to fast for 12 h prior to the test diet. They will also be instructed to avoid strenuous physical activity and alcohol consumption on the day before the test day, with this requirement reinforced through both in-person and WeChat-based instructions. Except for the differences in the random allocation sequence of the 5 test diets, the other study procedures across the 3 periods are identical, such as blood glucose monitoring, safety evaluation, duration of the washout period, and provision of balanced dinners.

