#### Population-level N-of-1 trial analysis

For the population-level assessment of the PPGR to different staple foods, a Bayesian generalized linear mixed regression model will be used to aggregate the results from multiple *N*-of-1 trials at the population level, incorporating both between-individual and within-individual variations. Individual regression models will be linked using a random-effects model, assuming that the individual-specific regression coefficients follow a normal distribution centered on the population’s average coefficient. Noninformative priors will be used to define the variance distribution of the parameters, ensuring the robustness of the analysis. The threshold for posterior probabilities will be set at 80%. Additionally, the posterior probability of the mean differences exceeding the MCID will be evaluated.

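### Stand-alone flat-prior analyses with three meals per food cannot by themselves show that responses differ between people, and no individual-level false-claim rate is given

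*Protocol article*

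**What the plan says.** Each participant eats each of five staple foods once per period: "The study consists of 3 periods, each of which comprised 5 test days" (Study procedures). That gives three meals per food.

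Under Individual-level N-of-1 trial analysis, a regression with food effects is fitted for the individual, and "Noninformative prior distributions will be incorporated into the model due to uncertainty regarding prior knowledge". The paragraph ends: "The threshold for posterior probabilities will be set at 80" (per cent). The next paragraph estimates, "sequentially using each staple food as a reference", the probability that the difference from the other four foods exceeds the MCID: "we define the MCID for PBGP as 0.78 mmol/L". Those probabilities are averaged, with weights, into the WGRS. The Discussion bases each patient's dietary recommendation on the WGRS, and the Exploratory analysis uses it as the microbiome outcome.

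The individual models are linked only under Population-level N-of-1 trial analysis, "assuming that the individual-specific regression coefficients follow a normal distribution centered on the" population average.

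The Sample size estimation section reports a type I error of 2.0%, for the population effect. The Statistical hypotheses section nevertheless poses a null for each participant over any two foods, and the Abstract states that "this study is anticipated to reveal substantial interindividual variations in PPGR".

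**The concern.** With three meals per food, the standard error of a within-person difference between two foods is larger than the MCID. A flat prior takes the observed difference at face value, and each person is examined over 20 directed comparisons. Chance can then look like a personal response.

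The trial's main interest is whether people differ. A list of individual results in which some participants show a difference and others do not would be expected even if everyone responded identically. Such a list could be read as the anticipated interindividual variation, and the inflated probabilities would carry over into the size of the WGRS.

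**Working it through.** **The plan's own error figure.** The plan states 86.0% power and 2.0% type I error at 14 participants for the population effect (80% posterior probability of exceeding 0.78). A flat-prior approximation with effect 2.4 gives 91.7% and 2.8% if 2.5 is the SD of individual differences, and 78.6% and 5.1% if 2.5 applies to each food separately. Priors and the meaning of the 2.5 are not given and the two versions bracket the stated power, so the plan's figure is not called wrong. It says nothing about the individual level.

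**Inputs.** Five foods, three meals each; "a within-individual SD of 1.2 mmol/L" (Sample size estimation); MCID 0.78; threshold 80%; noninformative prior.

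**One comparison, foods identical.**
- SE of a difference = 1.2 × √(2/3) = 0.980 mmol/L.
- Observed difference needed to pass = 0.78 + 0.8416 × 0.980 = 1.605 mmol/L.
- Chance of passing = P(Z > 1.605/0.980) = P(Z > 1.638) = 5.1%.

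**All 20 directed comparisons in one participant.** At least one passes when the range of the five food means exceeds 1.605. The SE of a mean is 1.2/√3 = 0.693, so the studentized range must exceed 1.605/0.693 = 2.316. For five means this has probability 47.3% with SD known, and 46.6% by simulation with SD estimated on 10 df. Expected participants affected: 14 × 0.473 = 6.6. Expected false claims per participant: 20 × 0.051 = 1.0. The range calculation allows for correlation; treating the 20 as independent would give 64.7%.

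**Dependence on the within-person SD.** 0.8 gives 25%, 1.0 gives 37%, 1.5 gives 57–58%.

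**Dependence on how the 80% is read** (foods identical, SD 1.2):

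| 80% applied to | Participants with at least one claim |
|---|---|
| each pair, difference > 0.78 | 47% |
| each food against the mean of the other four, > 0.78 | 16% (higher only), 26–27% (either direction) |
| each pair, difference > 0 | about 90% |
| any equally weighted WGRS | about 6% |

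**A common effect, no heterogeneity.** If everyone had the same true difference of 2.4 between two foods, the pair would pass with probability Φ((2.4 − 1.605)/0.980) = Φ(0.811) = 79%. About 0.21 × 14 = 3 participants would miss the threshold by chance and look different from the rest.

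**Stand-alone against partially pooled, by simulation.** The SD is that of true between-food differences across people. A claim is false if the true difference does not exceed 0.78; sensitivity is the share of true differences above 0.78 that are claimed.

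| SD of differences | Measure | Stand-alone | Pooled |
|---|---|---|---|
| 0 | participants with any claim | 46–47% | 0.1–0.3% |
| 1.0 | false share of claims | 31% | 16% |
| 1.0 | sensitivity | 0.40 | 0.13 |
| 2.5 | false share of claims | 6.4% | 4.9% |
| 2.5 | sensitivity | 0.68 | 0.64 |

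The pooled figures at SD 1.0 move by a few points with the prior on the heterogeneity SD.

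**Ranking by WGRS** (equal weights). The lowest-WGRS food is truly the best in 54% of participants stand-alone against 52% pooled at SD 1.0, and in 77% under both at SD 2.5. Pooling shrinks one person's five foods by a common factor, so their order hardly moves.

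**The case against.** Several points against the concern stand.

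- A reader might infer that the plan applies the 80% threshold to every ordered pair. It does not say so. The threshold sentence precedes the MCID paragraph, and the population section introduces the MCID probability as an additional quantity. The pairwise reading is natural because that is the only posterior probability defined at the individual level, but the 47% depends on it.
- A reader might infer that nearly half of this trial's participants will receive a false finding. The 47% requires identical foods. The plan assumes a rice–pasta difference of 2.4 and a between-individual SD of 2.5. If that SD is one of between-food differences, few claims are false under either analysis.
- A reader might infer that the dietary recommendations are wrong and that pooling would repair them. Recommendations use the WGRS, which has no cut-off, and pooling barely changes the food it favours.
- Stand-alone analysis is a legitimate N-of-1 approach. Pooling assumes exchangeable normal effects, estimates their spread from 14 people, and pulls atypical responders towards the average.
- Credible intervals are also reported, and the Discussion says that the Bayesian model carried individual-level variability through random effects.

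The last point does not dispose of the matter. The Discussion does not say which model it means, and the two analysis sections place the linkage only at population level. Nor does the plan's assumed heterogeneity settle it, because heterogeneity is what the trial sets out to investigate.

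**Conclusion.** The concern holds in a limited form. Stand-alone individual results cannot by themselves establish interindividual variation, and the plan gives no individual-level false-claim rate. With identical foods, within-person SD 1.2 and the pairwise MCID reading, about 47% of participants would show at least one apparent difference (25% to 58% for SDs of 0.8 to 1.5). If true differences vary with SD 2.5, the effect is small: 6% of claims false against 5% with pooling. What needs correcting is the strength of individual claims and the size of the WGRS, rather than the order of foods within a person. The documents do not support the stronger statement that the rule reports personal differences regardless of the truth: even with identical foods, just over half of participants would show none.

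**What to change.** 1. Base the conclusion on interindividual variation on the posterior of the food-by-person heterogeneity SD from the planned population-level hierarchical model.
2. Report each participant's partially pooled contrasts, probabilities of exceeding the MCID and WGRS from that model beside the stand-alone fits. Mark individual differences that appear only in the stand-alone fit as not robust.
3. State which posterior probability the 80% threshold governs at the individual level, and report the simulated individual-level false-claim rate for that rule.
4. Say which model the random-effects statement in the Discussion refers to.

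The cost is analysis code and a few sentences; no change to design or data collection is needed. The downside is lower sensitivity of the pooled estimates: 0.40 to 0.13 at SD 1.0, but only 0.68 to 0.64 at SD 2.5. That is why the stand-alone fits should stay in the report. Raising the stand-alone threshold is an alternative without pooling: with identical foods, 90%, 95% and 97.5% would leave about 23%, 10–11% and 5% of participants with a claim.
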